**Methods:**

This prospective, multicenter cohort study plans to enroll 2000 patients with AIS within 14 days of symptom onset from 30 hospitals across China. Eligible patients will be followed up for 6 months after initiating medication treatments. The primary outcome will be the change in the National Institute of Health Stroke Scale score from baseline to outpatient follow-up. The secondary outcomes include overall mortality, stroke recurrence, new-onset major vascular events, global disability, and improvement of traditional Chinese medicine syndrome in 6 months. Adverse events or clinically significant changes in vital signs and laboratory parameters, regardless of the severity, will be recorded during the trial to assess the safety of DZHJTI. An augmented inverse propensity weighted estimator will be used to reduce variability and improve accuracy in average treatment effects estimation.

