### Data Collection and Monitoring

Trained research personnel at each participating site will collect baseline data during patient admission, including prehospital care and treatment, prestroke symptoms, and the NIHSS. They will also conduct assessments using the prestroke modified Rankin Scale scores and Barthel Index. Patient information, including demographics, medical and family history, physical examination, auxiliary examination, risk factor assessment, and clinical diagnosis, will be obtained from medical records. The classification of stroke etiology, related complications, and new cerebrovascular events will be documented, and the etiology of AIS will be determined according to the Trial of Org 10172 in Acute Stroke Treatment criteria [17]. Besides standard therapies, the administration of DJHJTI during hospitalization will be documented by the research team.

The collection and reporting of data will use a secure electronic data capture (EDC) system that follows the current clinical protocol and provides each patient with a unique ID. Authorized research personnel can access the EDC system both on personal computers and smartphones, enabling them to complete data collection during daily ward rounds. An overview of the measurement data collection schedule is shown in Table 1. In the EDC system, personal identifiers such as names, ID numbers, and contact information are removed or replaced with unique codes to ensure participant anonymity.

**Table 1 table1:** Schedule of assessments in the cohort study.

Participant assessment	Time point and form				
	Baseline (acute phase)		Follow-up 1	Follow-up 2	Follow-up 3
	Admission	Discharge	1 month	3 months	6 months
	Visit	Visit	Visit or telephone interview	Visit or telephone interview	Visit or telephone interview
Eligibility screen	✓^a^				
Informed consent	✓				
Demographic and anthropometric data	✓				
TCM^b^ questionnaire	✓				
NIHSS^c^	✓	✓			
mRS^d^	✓	✓	✓	✓	✓
BI^e^			✓	✓	✓
Laboratory examination	✓	✓	+^f^	+	+
Imaging examination	✓	✓	+	+	+
Admission status		✓			
Discharge status		✓			
Follow-up interview			✓	✓	✓
AE^g^		+	+	+	+
Outcomes		+	+	+	+

^a^Required data.

^b^TCM: traditional Chinese medicine.

^c^NIHSS: National Institutes of Health Stroke Scale.

^d^mRS: modified Rankin Scale.

^e^BI: Barthel Index.

^f^Optional data to be collected based on the actual occurrence of related events in patients.

^g^AE: adverse events.

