### Follow-Up Procedures

All patients will be identified and followed up using individual identity cards, which are mandatory for all Chinese citizens, enabling unambiguous linkages. Research personnel will conduct regular face-to-face or telephone follow-up at 1, 3, and 6 months after stroke onset. Information on patient outcomes, including mortality, functional status, activities of daily living, cognitive function, and cardiovascular or cerebrovascular events, will be obtained during follow-up. Mortality will be confirmed through a death certificate issued by the local civil registry or the attending hospital. New cardiovascular or cerebrovascular events requiring rehospitalization will be verified by the discharge diagnosis. In the absence of hospitalization, a committee responsible for determining end points will evaluate suspected recurrent cardiovascular or cerebrovascular events [18].

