### Outcomes

In this study, the primary outcome will be the distribution of scores on the NIHSS before and after treatment among patients. Secondary outcomes will be assessed at different follow-up visits and will include death, a composite of new clinical vascular events, neurological function, and improvement of traditional Chinese medicine syndrome. Safety assessment will be performed by monitoring adverse events. The complete study outcomes are illustrated in Table 2.

**Table 2 table2:** Outcome variables and definitions.

Outcome variables		Definitions

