**Secondary outcomes**		
	Overall mortality	—^b^
	Stroke recurrence	—
	New-onset major vascular events	Major adverse vascular events include ischemic stroke, hemorrhagic stroke, transient ischemic attack, myocardial infarction, and vascular-related death
	Global disability	Measured by BI^c^ and mRS^d^ scale
	improvement of TCM^e^ syndrome	Measured by TCM questionnaire
	Adverse events	Undesirable experiences occurring to participants during the trial are considered to be related to the DJHJTIf

^a^NIHSS: National Institute of Health Stroke Scale.

^b^Not available.

^c^BI: Barthel Index.

^d^mRS: modified Rankin Scale.

^e^TCM: traditional Chinese medicine.

^f^DZHJTI: Dazhu hongjingtian injection.

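### Table 1 schedules the TCM questionnaire only at admission, although a secondary outcome is improvement on that questionnaire over 6 months

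*Protocol article*

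**What the plan says.** **TCM syndrome.** The Abstract (Methods) lists among the secondary outcomes "improvement of traditional Chinese medicine syndrome in 6 months". Table 2 names the instrument: "Measured by TCM questionnaire". The Outcomes section states "Secondary outcomes will be assessed at different follow-up visits" and includes improvement of TCM syndrome in the list that follows. The Abstract's Objective also names TCM syndrome within the study's primary aim.

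Table 1 (Data Collection and Monitoring) has five time points: admission, discharge, and 1, 3 and 6 months. The row "TCM^b^ questionnaire" is ticked at admission and nowhere else. A general row for outcomes carries a plus sign at discharge and at each of the three follow-ups. The footnote defines that sign as "Optional data to be collected based on the actual occurrence of related events in patients".

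Follow-Up Procedures describes what is gathered after discharge: "Information on patient outcomes, including mortality, functional status, activities of daily living, cognitive function, and cardiovascular or cerebrovascular events, will be obtained during follow-up". TCM syndrome is not among the items named.

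**Barthel Index.** The text on admission data says "They will also conduct assessments using the prestroke modified Rankin Scale scores and Barthel Index". Table 1 leaves the index blank at admission and discharge and ticks it at 1, 3 and 6 months. Table 2 defines global disability as "Measured by BI^c^ and mRS^d^ scale", without reference to a change from baseline.

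**The concern.** An improvement is a difference between two occasions. If sites work from Table 1, each patient contributes one TCM score, taken at admission, and there is nothing to subtract it from. The planned analysis could not repair this: the Statistical Analysis section proposes multiple imputation for missing covariates, and neither imputation nor the AIPW estimator can supply an outcome that was collected in nobody. Recruitment began in November 2022, so a patient who passes the 6-month contact without the questionnaire cannot be recovered later.

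The Barthel Index shows the opposite pattern. The text places it at admission and the table does not, so a site cannot tell whether an admission value is wanted.

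**Working it through.** The plan states no figure on this point, so the check sets the schedule against the outcome definitions.

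**1. Is the single tick an artefact of the extracted table?** Neighbouring rows keep sensible columns: NIHSS is ticked at admission and discharge, mRS at all five time points, and the follow-up interview at 1, 3 and 6 months. In any case the TCM row has one tick in total. Wherever that tick belongs, one measurement gives no change score.

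**2. Count of required TCM scores per patient.**

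| | Admission | Discharge | 1 month | 3 months | 6 months |
|---|---|---|---|---|---|
| TCM questionnaire (Table 1) | required | none | none | none | none |
| Needed for improvement over 6 months | yes | at least one score somewhere in these four columns | | | |

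Scheduled: 1. Needed: at least 2, one of them after admission. Required scores after admission: 0. Table 1 groups discharge under the baseline (acute phase) heading, so there are either three or four later contacts depending on how discharge is classed. The count is 0 either way.

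**3. Does the general outcomes row supply the second score?** It is marked only with the optional sign, which the footnote ties to the occurrence of related events. That suits deaths and vascular events. It does not oblige a site to repeat a questionnaire in every patient. The other scales used as outcomes (NIHSS, mRS, Barthel Index) each have their own row with required ticks after admission. The TCM questionnaire has its own row and no such tick.

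**4. Does the follow-up text supply it?** The list in Follow-Up Procedures does not name TCM syndrome. The list is introduced as inclusive, so it does not rule out a TCM assessment, but it does not schedule one.

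**5. Barthel Index.** Required entries in Table 1: 3 (1, 3 and 6 months), with 0 at admission, against one admission assessment in the text. The sentence in the text does not settle whether the word prestroke governs both scales or only the Rankin score. Under either reading Table 1 has no matching entry. The outcome in Table 2 is not a change score, so it can be computed from the three scheduled values.

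**The case against.** The strongest reply is that Table 1 is introduced as an overview and should not override the text. The Outcomes section says that secondary outcomes are assessed at follow-up visits and names TCM syndrome among them, and follow-up interviews are required at 1, 3 and 6 months. The investigators clearly intend a later assessment, and the case report form may well contain one.

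This stands as far as it goes. A reader might infer from Table 1 that every TCM change value in the study is missing. The documents do not support that: they do not show what sites collect, and the Outcomes text points the other way. But the intention stated there is not carried into the schedule, and nothing else in the article fixes a time at which the questionnaire is repeated. Nor is this an omission that a condensed article may leave to the full protocol, because the schedule and the outcome definition are both printed and they disagree.

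On the Barthel Index, a reader might infer that the comparison loses a strong prognostic covariate, and that collecting it would reduce variance by a stated amount or remove confounding through prestroke function. The documents give no correlation from which to derive such a figure. The exclusion criteria remove patients who were not independent in daily activities before the stroke, so a prestroke index would probably vary little. NIHSS and mRS are already required at admission, and the text also lists a prestroke Rankin score. The covariate list may properly sit in the statistical analysis plan, which is not shown.

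**Conclusion.** The contradiction holds. Table 1 provides for one TCM score per patient and none after admission, while the Abstract, the Outcomes section and Table 2 require at least one later score. Followed as written, the schedule makes this secondary outcome impossible to compute. The conclusion rests on reading the optional mark as its footnote defines it. Whether data are actually being lost depends on the case report form.

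One of the listed secondary outcomes is affected. The NIHSS primary outcome and the sample size are untouched.

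The Barthel Index mismatch is real but minor. Groups can still be compared on it at 1, 3 and 6 months, and no size is attached to it.

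**What to change.** **TCM questionnaire.** Take one of three routes, according to what sites now do:

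- Mark the questionnaire in Table 1 as required at 6 months, and also at discharge, 1 month and 3 months if the outcome is to be read then.
- If the case report form already repeats it, correct Table 1 to match.
- If no later assessment is intended, remove the outcome from the Abstract (Objective and Methods), the Outcomes section and Table 2.

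The first route costs one questionnaire at contacts that already take place. Table 1 allows follow-up by telephone, so the sponsor should confirm that the questionnaire can be given that way. Any patients already past follow-up without it would stay missing, and the report should say how many there are.

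**Barthel Index.** Reconcile the admission text with Table 1, and state whether an admission entry records prestroke or current status. This is an edit to the text or the table and, if the entry is kept, one more scale at admission.

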### Treatment Regimens

All patients will receive current guideline-recommended treatments according to *Chinese Guidelines for the Diagnosis and Treatment of Acute Ischemic Stroke 2018* [15]. The most commonly used medications and treatments include intravenous thrombolysis drugs, antiplatelets, anticoagulants, drugs for volume expansion, neuroprotectants, medicines for improving cerebral blood flow, and traditional Chinese medicine. Cases will be recruited from patients who receive DZHJTI according to the physician’s order. The DZHJTI will be manufactured and supplied by Tonghua Yusheng Pharmaceutical Co, Ltd (approvals Z20060361 and Z20060362), with identical appearance, color, and flavor. The fingerprint-based quality control and ingredient identification met the Chinese pharmacopeia’s reference requirements (detailed information is provided in Multimedia Appendix 1). The administration and dosage of DZHJTI will be determined by the attending physicians based on the patients’ medical history and clinical manifestations.

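### Table 1 makes adverse-event recording optional and event-triggered, which does not secure the promise to record events of any severity or ensure that no event can be told from not asked

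*Protocol article*

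**What the plan says.** Safety is a stated aim of the study (Abstract, Objective). The Abstract's Methods paragraph makes the commitment: "Adverse events or clinically significant changes in vital signs and laboratory parameters, regardless of the severity, will be recorded during the trial". The Outcomes section adds: "Safety assessment will be performed by monitoring adverse events".

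Table 1, under Data Collection and Monitoring, uses two marks. A check mark means "Required data" (footnote a). A plus sign means "Optional data to be collected based on the actual occurrence of related events in patients" (footnote f). The adverse-event row has a plus sign at discharge and at 1, 3 and 6 months, is blank at admission, and has no check mark anywhere. The modified Rankin Scale, the Barthel Index and the follow-up interview have check marks at 1, 3 and 6 months.

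Follow-Up Procedures sets the contacts: "Research personnel will conduct regular face-to-face or telephone follow-up at 1, 3, and 6 months after stroke onset". It then gives their content: "Information on patient outcomes, including mortality, functional status, activities of daily living, cognitive function, and cardiovascular or cerebrovascular events, will be obtained during follow-up". Adverse events are not named.

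**The concern.** An event-driven form is sound when something obligatory triggers it. If every patient is asked the same question and the form is opened on a positive answer, an empty form means no event. If no question is required, an empty form may mean that there was no event, that the patient did not mention one, or that nobody asked. The counts then depend on how readily events come to light at each site and in each group.

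That matters more here than in a blinded trial. "Cases will be recruited from patients who receive DZHJTI" on the physician's order, and no blinding is described, so it is a fair inference that staff and patients know who had the injection. That knowledge could raise recording in the injection group, through closer attention, or lower it, if minor reactions are regarded as expected. The event rate and the comparison with controls would both be exposed to this, and the data as scheduled could not show whether it had happened.

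**Working it through.** The document gives no adverse-event rate and no figure for completeness of recording, so there is no figure of its own to reproduce. The check is mainly a comparison of passages.

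**Step 1: the marks in Table 1.**

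| Row | Discharge | 1 month | 3 months | 6 months |
|---|---|---|---|---|
| Modified Rankin Scale | required | required | required | required |
| Barthel Index | none | required | required | required |
| Follow-up interview | none | required | required | required |
| Adverse events | optional | optional | optional | optional |
| Outcomes | optional | optional | optional | optional |

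Adverse-event recording is required at 0 of the 4 time points where it appears.

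**Step 2: what could trigger each optional form.** The Outcomes row has the same mark, so the mark alone does not mean that nobody asks. What differs is the supporting text. Follow-Up Procedures says that mortality and cardiovascular or cerebrovascular events are obtained at follow-up. It then provides death certificates, discharge diagnoses and an end-point committee to confirm them. For adverse events the article states no enquiry and no verification step.

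**Step 3: commitment against schedule.** The abstract promises recording of adverse events, and of significant vital-sign and laboratory changes, at any severity. The schedule makes the adverse-event form optional, and laboratory examination is also optional after discharge. The promise may be kept in practice, but the schedule does not secure it.

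**Step 4: illustration of scale.** The group size of 1000 (Sample Size) and the two-sided 0.05 level (Statistical Analysis) are from the document. The true rates and recorded proportions are assumptions. Let the true rate t be equal in both groups, with 90% of events recorded under the injection and 60% in controls. The observed rates are p1 = 0.90t and p2 = 0.60t, and their ratio is 0.90/0.60 = 1.5 whatever t is.

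For t = 10%, p1 = 9% and p2 = 6%:

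- SE = √(0.09 × 0.91/1000 + 0.06 × 0.94/1000) = 0.01176
- z = 0.03/0.01176 = 2.55

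The chance of P < .05 when no true difference exists is about Φ[(|p1 − p2| − 1.96 × SE0)/SE], where SE0 is the standard error from the pooled proportion. Holding the injection group at 90% recorded:

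| Recorded in controls | Observed ratio | t = 2% | t = 5% | t = 10% |
|---|---|---|---|---|
| 90% | 1.0 | 5% | 5% | 5% |
| 75% | 1.2 | 8% | 13% | 23% |
| 60% | 1.5 | 20% | 42% | 72% |
| 45% | 2.0 | 41% | 80% | 98% |

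Swapping 90% and 60% between the groups gives a ratio of 0.60/0.90 = 0.67 and z = −2.55 at t = 10%, a spurious benefit. Equal recording at 60% leaves the ratio at 1.0 but reports 6% where the truth is 10%. These figures show what unequal recording would do if it occurred. They do not show that it will.

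**The case against.** The strongest reply is that the plus sign simply marks event-driven forms. The Outcomes row has it at the same four time points, and nobody would conclude from this that deaths are not asked about. This stands: a reader might infer from the contrast with the required rows that the authors deliberately set adverse events apart, and the table does not support that.

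A reader might also infer that no contact exists at which adverse events are asked about. That is not established either. The interview is required at 1, 3 and 6 months, and the list of what it obtains is introduced as examples, so it is not closed. Table 2 places adverse events among the secondary outcomes, and the Outcomes section says that secondary outcomes are assessed at follow-up visits. The abstract separately commits to recording. During the hospital stay, data are collected on daily ward rounds, and laboratory tests are required at admission and discharge. For these reasons the further inference that the safety results would be uninterpretable goes too far.

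It can also be said that the wording of a safety question belongs to the case report form or operating procedures, which are not shown. That is true of the wording. Whether recording is required or optional, however, is fixed in this article, and a full protocol that required the enquiry would conflict with Table 1.

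Lastly, Table 2's definition is a separate obstacle to comparison: "Undesirable experiences occurring to participants during the trial are considered to be related to the" study injection, a condition that controls cannot meet. Correcting it would not settle how events are ascertained, and the illustration above presupposes a definition that applies to both groups.

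**Conclusion.** The point holds as an inconsistency and an unsecured step in the schedule. Recording is optional and event-triggered at all four time points where the adverse-event row appears, the follow-up text does not name adverse events, and no stated enquiry or verification step would trigger the form. This does not secure the abstract's commitment, and it does not ensure that absence of an event can be told from absence of a question.

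Different ascertainment between the groups is a possibility, resting on the inference that treatment is known to staff and patients. Its size and direction cannot be taken from the documents, and the illustrative error rates rest wholly on assumed recording proportions. The point is worth acting on because safety is a stated aim and the correction is cheap.

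**What to change.** Reconcile the Abstract, Table 1 and Follow-Up Procedures:

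- In Table 1, make a standard yes/no adverse-event enquiry required at discharge and at 1, 3 and 6 months, worded identically for both groups. Open the detailed form only on a yes.
- In Follow-Up Procedures, add adverse events to the information obtained at each contact.
- Count a patient as event-free at a contact only where a no was recorded, and treat a blank as missing.

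The cost is one mandatory item in the electronic data capture system at contacts that already take place, and a line in the training material. The downside is a higher recorded rate of mild events. Recruitment began in November 2022, so the date of the change should be documented, because contacts before it will lack the item.

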### Follow-Up Procedures

All patients will be identified and followed up using individual identity cards, which are mandatory for all Chinese citizens, enabling unambiguous linkages. Research personnel will conduct regular face-to-face or telephone follow-up at 1, 3, and 6 months after stroke onset. Information on patient outcomes, including mortality, functional status, activities of daily living, cognitive function, and cardiovascular or cerebrovascular events, will be obtained during follow-up. Mortality will be confirmed through a death certificate issued by the local civil registry or the attending hospital. New cardiovascular or cerebrovascular events requiring rehospitalization will be verified by the discharge diagnosis. In the absence of hospitalization, a committee responsible for determining end points will evaluate suspected recurrent cardiovascular or cerebrovascular events [18].

